#### Coaching

Coaches will be allied health professionals with previous experience in coaching families of children with developmental differences in healthcare or disability settings. They will receive training on the FF programme content to ensure familiarity with the materials for parents. In addition, they will be trained on procedures such as booking of sessions, scope of the coach role and elements of sessions to be documented (eg, date, duration, parent goals and identified actions), as well as the principles underpinning the coaching model in this trial, which include:

Relationship based, collaborative and family centred.Goal generating, in line with the family’s needs, priorities, preferences and resources.Goals focused on overall child and family functioning, well-being or participation.Aiming to optimise empowerment and participation of the family as they provide support for their child with developmental regression and other family members.Coaching conducted in a strengths-based approach with joint planning, observation, reflection, action and feedback.

The role of the coach is to create opportunities for the parents to establish goals important to them and their family, reflect on what information and resources that would assist progress towards the goal, and to encourage parents to identify actions they can take. When parents identify goals that are related to content within the online programme, the coach will support reflection and discussion of the relevant online content and guide the parent to determine ways in which potential strategies can be implemented into family routines. Coaches will not provide direct therapy for the child and will recommend families consult with their community-based therapists for child-related therapy questions.

A fidelity checklist for the coaching approach will be developed and will include the expected coaching behaviours that reflect the key principles named above. Where the participant provides consent to audio-recording or video-recording, the coach will record the session to self-evaluate performance on the fidelity checklist post session. These recordings will be randomly sampled and rated by a research team member with experience in this coaching approach to ensure fidelity to the protocol and consistency across coaches in approach.

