### Study procedures

#### Enrolment and randomisation

Eligible parents of children assessed through the research-embedded Developmental Regression clinic will be provided with information about the intervention trial and invited to participate. For those who consent to this study, if data on the outcome measures were collected as part of their first assessment or a follow-up review at the clinic within the past 6 months (whichever is closer to their study enrolment), the data will be transferred and used as their baseline data (T0) in the trial. Specifically, direct identifiers (eg, names) will be replaced by a code before participant data are transferred to a research-only database using REDCap, a secure, web application to support data capture.^40^ A 1:1 randomisation allocation sequence will be computer-generated within REDCap to allocate parent participants to the FF group or Coaching+FF group, thereby ensuring that participants, coaches, trial coordinator, outcome assessors and the research team analysing the data are concealed from the group assignment until baseline assessment and allocation are completed. Outcome assessors (clinicians completing assessments of the child) will remain blinded to group allocation across the assessment timepoints.

Participants will also complete post-intervention (T1) and follow-up (T2) assessments via online questionnaires hosted in REDCap. Figure 2 outlines the participant flow.

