#### Blinding

To minimise bias and possible contamination, the coaches in this trial will be employed by Monash University and will be independent of the Developmental Regression clinic. The coaches working with the participants in the Coaching+FF group will not be in contact with participants in the FF group.

The FF programme will be implemented through the Induk (https://induk.io/) technical infrastructure, which securely encodes participant accounts using anonymous unique identifiers for each participant. This mediated approach ensures that potential bias from administrators or the research team is effectively eliminated. Given that this is a pragmatic trial, it is not possible or appropriate to blind parent participants (ie, parents would know if they would access coaching).

The questionnaires for collecting primary outcome data and other parent-reported outcomes are administered and captured by REDCap, thereby maintaining the blinding of researchers to treatment allocation and ensuring consistent data collection.

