#### Sample size

This study will enrol eligible families of children seen at Monash Children’s Developmental Regression Clinic who have consented to taking part in this intervention trial.

As there was a lack of available effect size estimates for interventions targeting families of children with regression, we used effect sizes from online interventions that aimed to improve mental health, stress and well-being of parents of children with a disability or chronic medical condition.^20^ To calculate the sample size required for *F-*tests (analysis of covariance (ANCOVA) and analysis of variance (ANOVA)), G*Power 3.1.9.7 software was used.^41^ To detect a large effect (*f*= 0.5) in the primary outcome (ie, parental stress) with a power of 80% and α of 0.05 (two-tailed), a sample size of 43 parents is required. To allow an attrition of approximately 30% between baseline (T0) and follow-up assessment (T2), a sample size of 56 parents (28 per group) is required.

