### Data analysis

Missing data, participant dropout and loss to follow-up will be minimised through careful trial management. Additionally, the rates of missing data on individual data collection forms will be monitored at each time point throughout the study.

The primary analyses will be undertaken on an intention-to-treat basis. Participant characteristics, participant engagement and intervention usage, and coaching acceptability will be described. A 2 (Group)× 3(Time) repeated measure ANOVA will be applied to compare continuous scores for primary and secondary outcomes between the intervention and comparison groups.

To explore possible attrition biases, we will also conduct analyses to compare retained participants and those lost after baseline assessment, using *t*-tests for continuous measures and chi-square-tests for categorical variables (eg, gender, family socioeconomic and clinical factors). Qualitative data collected using semi-structured interviews (eg, transcripts) will be examined by thematic analysis.

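### The planned ANOVA makes no allowance for clustering by coach in the Coaching+FF arm; if outcomes differ by coach, the standard error is understated and the type I error may exceed 5%

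*Protocol article*

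**What the plan says.** Randomisation is by individual parent (Enrolment and randomisation): "A 1:1 randomisation allocation sequence will be computer-generated within REDCap to allocate parent participants to the FF group or Coaching+FF group". The Coaching+FF arm is offered up to twelve individual videoconference sessions over six months (Trial arms). Coaches are referred to in the plural, and a sample of recorded sessions is rated "to ensure fidelity to the protocol and consistency across coaches in approach" (Coaching). Coaches exist on one side of the comparison only (Blinding): "The coaches working with the participants in the Coaching+FF group will not be in contact with participants in the FF group".

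The Data analysis section names a single model for the primary and secondary outcomes, a 2 by 3 "repeated measure ANOVA will be applied to compare continuous scores for primary and secondary outcomes between the intervention and comparison groups". It has no coach term. The Sample size section contains no design effect. The article does not give the number of coaches, their caseloads, the rule that assigns parents to coaches, or an ICC.

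**The concern.** This is a partially nested design: outcomes can be correlated within coach in one arm, with no counterpart in the other. A repeated-measures ANOVA allows for correlation between the visits of one parent, but takes different parents as independent. If some coaches achieve more than others, parents who share a coach are alike, and the coached arm carries less information than its head count suggests.

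The article aims at realistic estimates of what coaching adds to the online programme. An interval that ignores coach-to-coach variation is too narrow for that general claim whenever the effect varies by coach, whether or not the average effect is zero. With few coaches, a nominally significant difference could reflect one particularly effective coach.

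**Working it through.** **1. The plan's own figures.** Inputs from Sample size: "To detect a large effect (*f*= 0.5) in the primary outcome", "with a power of 80% and α of 0.05 (two-tailed), a sample size of 43 parents is required", then "a sample size of 56 parents (28 per group) is required" after an allowance of about 30% attrition. A noncentral F calculation with λ = f²N = 0.25 × 43 = 10.75, numerator df 2, six cells and one covariate gives N = 43 (power 0.810). Then 43 × 1.3 = 55.9, which rounds to 56. Both figures reproduce without any clustering allowance.

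**2. Assumptions.** The article gives no values, so these are assumed: 2 to 6 coaches, equal caseloads, one coach per parent, ICC 0 to 0.10. Arm sizes are 28 (as randomised) and 20 (28 × 0.7 = 19.6, after the planned attrition).

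**3. Standard error.** With m parents per coach:

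- design effect in the coached arm: DE = 1 + (m − 1) × ICC
- true SE / ANOVA SE = √((1 + DE)/2), because only one of two equal arms is clustered

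With 28 per arm:

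- 4 coaches, ICC 0.02: m = 7, DE = 1.12, ratio √1.06 = 1.03
- 3 coaches, ICC 0.05: m = 9.33, DE = 1.42, ratio √1.21 = 1.10
- 2 coaches, ICC 0.10: m = 14, DE = 2.30, ratio √1.65 = 1.29

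A hand check of the error rate is 2 × (1 − Φ(1.96/ratio)). For the last case 1.96/1.285 = 1.525, giving about 12.7%.

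**4. Simulated type I error, two-group test at one time point, 28 per arm** (20,000 runs per setting; coach variance in the coached arm only; average coaching effect zero):

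| Coaches | ICC 0.02 | ICC 0.05 | ICC 0.10 |
|---|---|---|---|
| 2 | 6.4% | 8.8% | 13.4% |
| 3 | 6.1% | 7.5% | 10.1% |
| 4 | 5.7% | 6.7% | 8.8% |
| 6 | 5.5% | 6.1% | 7.2% |

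At ICC 0 the rate is 5% for any number of coaches, within simulation error.

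**5. The planned group-by-time test** (within-parent correlation 0.5 assumed; coach effect present after baseline only). With 28 per arm and 2 to 6 coaches the rates are 5.3% to 6.4% at ICC 0.02, 6.0% to 8.9% at 0.05 and 7.2% to 13.1% at 0.10. With 20 per arm:

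| Coaches | ICC 0.02 | ICC 0.05 | ICC 0.10 |
|---|---|---|---|
| 2 | 5.9% | 7.3% | 10.2% |
| 3 | 5.8% | 6.9% | 8.3% |
| 4 | 5.6% | 6.1% | 7.5% |
| 6 | 5.3% | 5.8% | 6.3% |

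Two simulation standard errors at a true 5% are 2 × √(0.05 × 0.95/20,000) = 0.3 points, so repeat runs differ by a few tenths. Allowing for that, 2 to 4 coaches give about 5.7% to 13% with 28 per arm and about 5.3% to 11% with 20 per arm.

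**6. Same effect expressed as sample size.** Multiplying the 43 by (1 + DE)/2, with m taken from 28 per arm: 43 × 1.037 = 45 (6 coaches, ICC 0.02), 43 × 1.208 = 52 (3 coaches, ICC 0.05), 43 × 1.65 = 71 (2 coaches, ICC 0.10).

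**The case against.** The strongest objection is that the inflation is conditional, and it stands. A reader might infer that the type I error does exceed 5%. The article does not support that: it needs an ICC above 0 and several parents per coach, and neither figure is given. If coaching had no effect with any coach, coaches would add no variance and the rate would stay at 5%. The inflation arises when the effect averages zero but varies by coach. At ICC 0.02 with 4 to 6 coaches the excess is under one point.

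A reader might also take the consistency ratings as the protocol's own prediction that coaches will differ in outcome. They are not. They are a control intended to limit differences in approach, and they may reduce the ICC. Equally, they do not show it to be zero for support that is individualised and built on a relationship.

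One coach per parent is likewise not stated. The Trial arms section refers to a parent's coach in the singular, but no assignment rule is given and scheduling is flexible. If parents can see more than one coach, a simple nested term would be the wrong model.

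It can also be said that sensitivity analyses belong in a statistical analysis plan, which is not shown and could add a coach term. That holds for the detail. It does not remove the point, because the article names the model for the primary outcome and that model assumes independent parents.

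Finally, with two or three coaches the coach variance is poorly estimated, so the remedy is weakest where the problem is largest. This is why the fix leaves the primary model alone and has a fallback.

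**Conclusion.** The point holds in conditional form. Several coaches serve one arm only, and neither the stated ANOVA nor the sample size allows for it. If the coach ICC is above 0, precision is overstated. With 28 per arm, the standard error is understated by a factor of 1.03 (4 coaches, ICC 0.02) to 1.29 (2 coaches, ICC 0.10). The group-by-time error rate is then about 5.7% to 13% with 28 per arm and about 5.3% to 11% with 20.

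These figures rest on assumed numbers of coaches and ICCs, equal caseloads, one coach per parent and a within-parent correlation of 0.5. They show how much the result could depend on coaches and are not a forecast of the trial's actual error rate. The upper end needs two coaches, ICC 0.10 and all 28 coached parents retained. The point is a worthwhile, inexpensive improvement and not a reason to replace the primary model.

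**What to change.** Keep the primary model and add the following before analysis:

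- Record the coach or coaches seen by each parent, linked to the study code. The session elements that the article lists as examples do not include coach identity, so name it explicitly.
- Prespecify a sensitivity analysis of the primary outcome with a coach random effect in the Coaching+FF arm only, arm-specific residual variance and small-sample degrees of freedom. If parents can see more than one coach, adapt the random-effect structure.
- Report the number of coaches, their caseloads and the estimated ICC.
- If coaches are too few to estimate the variance, report the primary interval with its standard error multiplied by √((1 + DE)/2) for a stated range of ICCs, for example 0.01, 0.05 and 0.10. With 28 per arm and two coaches the multipliers are 1.03, 1.15 and 1.29.
- If the conclusion depends on that choice, limit it to the participating coaches.

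The cost is one recorded variable and one extra model. The downside is a wider interval and an imprecise coach variance when coaches are few. If the identifier is not kept, clustering cannot be examined later.

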### Risk monitoring

Given the security and privacy procedures outlined in this protocol, there is low–moderate risk to children/families of any harm, inconvenience, or discomfort resulting from participation in the trial. Information regarding potential risks, risk mitigation measures and contact helplines are included in the Participant Information and Consent Form. Further, a trauma-informed approach was applied in designing the online portal where participants access the FF programme. Specifically, features to guide participants on taking breaks from the material and information about supportive helplines and health services were identified to assist participants who might experience feelings of grief or trauma when engaging with the material. If coaches identify any issues of concern regarding a parent, they will recommend they access a relevant community service (eg, present to the local emergency department, contact their treating general practitioner or provide information on helplines). Coaches will have access to discuss any such issues with a senior psychologist on the research team if required. If an assessment shows a score that falls outside the normal limits, participants may be offered feedback, further support and referrals to relevant services.

A data monitoring committee was not considered, as this is a low-risk research study. All standard operating procedures will be documented and provided to research team members who are directly involved in the study. All risks and adverse events, including unexpected side effects, will be monitored and documented by the clinic/trial coordinator, who will act in accordance with the risk management plan. Any significant safety issue or protocol deviation that adversely affects participant safety or the ethical acceptability of the trial will be reported to the investigators and the relevant Human Research Ethics Committee. In the event of new risks or adverse events being identified, the risk management plan will be appended with a course of action. Protocol amendments are communicated to clinical and research team members by the clinic/trial coordinator through email notifications describing the changes and any impacts to operations. These email notifications will include the updated protocol and relevant updated study documents.

## Discussion

This study is the first to evaluate the effectiveness of an online programme with and without 1:1 health professional coaching, designed for families of children who have experienced developmental regression. The trial has several strengths including the pragmatic RCT design in which the trial is embedded within a routine clinical care environment. The blinding of healthcare providers collecting clinical data and outcome data helps to safeguard against potential bias. In addition, online coaching and the use of a flexible online platform to access the FF programme are expected to enhance accessibility. By integrating the insights from families with lived experience, advocates from lived experience agencies, and clinicians into the design of the programme and coaching approach, we have tried to ensure that the interventions are relevant to their needs and that potential risks or concerns are addressed in the design phase. Notwithstanding, given the clinical heterogeneity of the study’s population, it may be necessary to broaden the diversity of health service users (carers) who contributed their experiences and perspectives to the codesign of the online intervention. The additional features (eg, podcasts, audio files and videos) included in the FF programme may encourage engagement which will be measurable via the online portal. Together, these approaches will enable comparisons of the uptake and effectiveness of a self-guided programme for parents of children with developmental regression and a version of the programme that includes individualised coaching.

With this study being the first intervention trial for parents of children with developmental regression, we acknowledge limitations in relation to the study design. These include the lack of participant blinding to their treatment group, and the length and frequency of the follow-up assessments for capturing outcomes. Since baseline assessment may be conducted well before a participant begins accessing the programme or coaching, there is also a risk that variations in the time interval between the baseline assessment and the start of the intervention could allow external factors unrelated to the intervention to influence participants’ responses to intervention. Moreover, participants enrol in the trial one at a time, making it impractical to perform stratified randomisation. Nonetheless, we will conduct subgroup analyses where appropriate to explore potential variation in outcomes.

Participation in the FF programme and coaching requires an internet connection. While the online nature was intended to optimise accessibility, families without a stable internet, adequate data and/or a suitable electronic device may not be able to participate. Despite the implementation of participant engagement and retention strategies, there remains a risk of insufficient sample size. This could result in limited statistical power, potentially constraining the scope and robustness of the planned analyses.

The findings from this trial have the potential to inform future development of interventions for families of children experiencing developmental regression to improve outcomes for parents and their children in terms of mental health, family empowerment, quality of life and participation within their communities. In comparing self-guided FF to FF with coaching, the study will provide preliminary data on the uptake and effectiveness of the different versions of the FF programme for families caring for children with developmental regression, while addressing important questions about the differences between guided and unguided interventions. Additionally, this trial may help shape the design of future interventions for children with developmental regression.

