**Trial registration number:**

ISRCTN25513446.

STRENGTHS AND LIMITATIONS OF THIS STUDYThis will be the first study using a randomised controlled trial and mixed-methods design to assess the effectiveness of an online programme for reducing parental stress, with and without coaching, in parents of children with developmental regression.A key strength of the study is the codesign of the programme with an advocacy and research-driven non-profit organisation and families of children experiencing developmental regression, in partnership with clinician researchers.The time interval between onset of developmental regression and the start of the intervention will vary among participants. As participants enrol one at a time in this trial, it is impractical to use stratified randomisation based on different time intervals.While the implementation of strategies to recruit, engage and retain participants has been included, lower than expected recruitment would limit the scope of the analyses and conclusions.

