### Eligibility criteria

Parents of children aged between 1 and 15 years with loss of skills in one or more developmental domains (communication, motor, social engagement or daily living) within the 18 months prior to their first visit to the Developmental Regression clinic are the target population. Other eligibility criteria include residency in Victoria, Australia, comfort in reading English at Grade 7 level, access to an internet-enabled device and an active email account.

Participants are not eligible if: (1) the child’s history of loss of skills cannot be corroborated through developmental surveillance information, clinical assessment or review of video/audio recordings, or (2) the regression is judged to have occurred primarily in the context of significant environmental adversity such as documented abuse, neglect or severe household adversity or (3) the child’s condition warrants prioritisation of medical intervention and stabilisation over research participation.

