** *Other data* **				
Skill regression information	X			
Antenatal and pregnancy information	X			
Developmental history	X			
Physical and medical examination or history	X			
Support and services information	X		X	X
FF engagement				
FF acceptability				
Coaching engagement				
Coaching acceptability				

CGI-I, Clinical Global Impression Scale-Improvement; CGI-S, Clinical Global Impression Scale-Severity of illness; DASS-21, Depression Anxiety Stress Scales – short form; FES, Family Empowerment Scale; FF, Family Focus programme; FQOL, Beach Family Quality of Life Scale; HPAS, Health Promoting Activities Scale.

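### One-at-a-time enrolment is no obstacle to stratified randomisation, and subgroup analysis is the wrong response to varied timing; covariate adjustment would serve better

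*Protocol article*

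**What the plan says.** The strengths and limitations box names a source of variation: "The time interval between onset of developmental regression and the start of the intervention will vary among participants". It then says: "As participants enrol one at a time in this trial, it is impractical to use stratified randomisation based on different time intervals". The Discussion repeats the reason in general form, "participants enrol in the trial one at a time, making it impractical to perform stratified randomisation", and follows it with the response: "we will conduct subgroup analyses where appropriate to explore potential variation in outcomes".

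The Discussion also raises a second interval as a risk to how parents respond: "variations in the time interval between the baseline assessment and the start of the intervention could allow external factors unrelated to the intervention to influence".

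Other relevant statements in the protocol article:

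- Eligibility criteria: loss of skills must fall "within the 18 months prior to their first visit to the Developmental Regression clinic". Under Recruitment, both current and past attenders of the clinic may be invited.
- Enrolment and randomisation: clinic data collected "within the past 6 months (whichever is closer to their study enrolment), the data will be transferred and used as their baseline data". Allocation is 1:1 from a sequence generated in REDCap; no strata, blocks or minimisation are mentioned.
- Table 2: "Skill regression information" is collected at T0, ahead of allocation.
- Data analysis: a 2 (group) × 3 (time) repeated-measures ANOVA for primary and secondary outcomes, with no covariate named.
- Sample size: calculated for F-tests described as both ANCOVA and ANOVA.

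**The concern.** Sequential enrolment is the ordinary setting for stratified permuted blocks and for minimisation. Neither needs the whole sample to be known in advance, so the only reason given for not stratifying does not hold. A small sample could be a genuine reason, but the article does not offer it.

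The response does not match the problem either. Having named timing as a limitation, the article answers with subgroup analyses. These ask whether the treatment effect differs between kinds of family. They do not even out a chance difference between arms and do not remove its influence on the overall comparison. The tool that does is covariate adjustment, and the analysis as stated contains none for timing. At stake are precision and exposure to chance imbalance in a trial of 56 families.

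**Working it through.** **The plan's own figures.** With a noncentral F, λ = f²N, f = 0.5, α = 0.05 and power 80%, numerator df = 2 gives N = 42, or 43 with six cells and one covariate. The stated 43 is therefore reproduced. Numerator df = 1 gives 34. For attrition, 43 × 1.3 = 55.9, so 56. This point disputes neither figure and does not change the required N.

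**Can a stratum be known in time?** Regression information is collected at T0 and randomisation follows, so time from onset to randomisation is available for each family. The two intervals that the article names both end at the start of the intervention, which comes after allocation. Only the part up to randomisation can be a stratum or a baseline covariate.

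**Chance imbalance.** Assumption, as the documents give no prevalence: a two-level factor present in 28 of 56 families.

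- Simple randomisation: P(difference ≥ 20 percentage points) = 0.14; P(≥ 25 points) = 0.08.
- Arms forced to 28:28 (hypergeometric 56, 28, 28): the smallest possible difference above 20 points is 17/28 − 11/28 = 21.4 points, and P(≥ 21.4 points) = 0.18.
- Stratified blocks of 4 (simulation, 6,000 runs per scenario): no run reached 20 points. The 95th percentile of imbalance falls from about 26–28 points to about 4.
- Standardised continuous covariate: SE of the arm difference = √(4/56) = 0.27 SD, so P(> 0.25 SD) = 35% and P(> 0.5 SD) = 6%.

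**Effect on the comparison.** Assumptions: prevalence 50%, all 56 families analysed, one outcome time, true effect 0.8 SD. The documents do not give the factor's prognostic strength, so two values are shown.

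| Factor shifts outcome by | Simple, unadjusted | Simple, adjusted | Stratified, adjusted |
|---|---|---|---|
| 0.5 SD | 80% | 82% | 84% |
| 1 SD | 74% | 82% | 84% |

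Type I error under simple randomisation without adjustment was 5.4–5.5%, within simulation error of 5% (SE √(0.05 × 0.95/6000) = 0.3 points). Stratifying without adjusting gave 3.8% and 2.8%, which is conservative, so adjustment is needed even if strata are used.

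A 20-point imbalance moves the unadjusted arm difference by 0.20 × 0.5 = 0.1 SD, or by 0.20 × 1 = 0.2 SD. Read as a two-group contrast, the design effect is 2f = 1 SD.

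**Subgroup analysis.** Two subgroups by two arms gives 56/4 = 14 per cell. The SE of the interaction is √(4/14) = 0.53 SD. Two-sided power at 0.05 is 15% for an interaction of 0.5 SD, 31% for 0.8 SD and 45% for 1.0 SD. With 10 per cell after dropout it is 12%, 23% and 34%.

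**Baseline stress.** T0 is one of the three times in the ANOVA, so a group × time test works on change from baseline. For the T1 contrast with equal variances and correlation r, the variance is proportional to 2(1 − r) for change and 1 − r² for adjustment, a ratio of (1 + r)/2. Taking r from 0.3 to 0.7 (assumed), adjustment needs 65% to 85% of the variance of change.

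**The case against.** Four objections carry weight.

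- A reader might infer that time since regression onset is a known prognostic factor. The article says only that one interval varies and that the other could let outside influences in. It gives neither interval an effect on parental stress.
- A reader might infer that leaving out strata biases or confounds the result. It does not. Simple randomisation is valid on average, and not stratifying a single-clinic trial of 56 is a legitimate choice. With a 0.5 SD factor, adjustment gains only about 2 points of power.
- A reader might infer that nothing in the plan absorbs baseline differences. T0 stress is already a repeated measure in the ANOVA. A factor that shifts stress equally at all three times drops out of a group × time test; only one that changes the trajectory remains. The power table describes a single-time comparison and so shows more loss than that test would suffer.
- Covariates are often left to an analysis plan, and the mention of ANCOVA suggests that adjustment was contemplated.

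The first three limit the size of the point and stand. The last stands only in part: an unlisted detail would be no finding, but the article states both a model without covariates and a response to heterogeneity, and a better one exists for each. The limitation is openly disclosed and the subgroup analyses are described as exploring variation. That is to the article's credit, but it does not make the rationale correct.

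**Conclusion.** The rationale is incorrect in both places where it appears, and subgroup analysis does not address the limitation it is set against. The design is not invalid. Its cost is chance imbalance (about 14% for 20 points or more under simple randomisation, 18% for 21 points or more with forced 28:28) and some precision: about 2 points of power if the factor is worth 0.5 SD, about 8 if it is worth 1 SD.

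Those figures rest on an assumed 50% prevalence, assumed prognostic strengths, no attrition and a single-time comparison. The documents support no claim of bias, of an established prognostic factor, or of baseline stress being ignored. What remains is a wrong reason to correct and an inexpensive improvement to the stated analysis.

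**What to change.** 1. Delete the one-at-a-time rationale in the strengths and limitations box and in the Discussion, or replace it with a genuine small-sample reason.
2. Analyse post-baseline stress in a model that adjusts, for all participants, for baseline stress and for time from regression onset to randomisation. Do not use time to the start of the intervention, which falls after allocation. This would also bring the analysis into line with the ANCOVA named in the sample size section.
3. State this adjustment as the response to heterogeneity in timing, and label any subgroup analysis exploratory.
4. Optionally, stratify the remaining enrolments on one two-level version of time since onset. This needs a fixed cut, a new allocation list and an amendment during enrolment. It is a trade-off, as adjustment alone recovers most of the loss.

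Items 1 to 3 need a short text amendment and 1–2 model degrees of freedom. They require no new data and no change to randomisation.
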